#### 2.13.2. Sample Collection and Storage

Tumor biopsies will be collected during both screening colonoscopy and elective CRC surgery, and will be immediately placed in a sterile collection tube. Samples will then be taken to the Anatomic Pathology Service of the Virgen de la Arrixaca University Hospital for fixation and standard evaluations.

For stool sample collection, participants will be asked to bring their samples at baseline, the day before the surgery, and at the follow-up visit. Patients will be given an appropriate sterile collection container. If the sample is collected the day before the appointment, the patient will be asked to place the sample in the freezer until the following day. Once the sample is collected by the research staff, it will be weighed and then placed in the fridge a maximum of 4 h prior to snap-freezing in N_2_, and stored at −80 °C.

For blood sample collection, patients will be asked to fast for 12 h before the appointment. A specialized nurse will obtain two samples of 7.5 mL, one in a collection tube with clot activator for serum and one in a collection tube with EDTA for plasma isolation. Plasma and serum samples will be used for the determination of endotoxemia, intestinal permeability and inflammation markers.

The analysis of SCFAs in plasma/feces will be performed by gas chromatography-triple quadrupole mass spectrometry (GC-QqQ/MS).

All samples will be stored frozen at −80 °C at the Biobank of IMIB (registered at the Spanish Biobank Register of the Institute of Health Carlos III, ref num. PT17/0015/0038).

#### 2.13.3. Analysis of Gut and Intra-Tumoral Microbiota Composition

Analysis of the gut and intra-tumoral microbiota composition will be performed by 16 s rRNA gene sequencing in stool and biopsy samples, respectively. DNA extraction from stool samples will be performed using 200 mg of sample using the QIAamp DNA Stool Mini kit (Qiagen, Manchester, UK), following the manufacturer’s instructions. DNA extraction from FFPE tissue samples will be performed on three sections of 10 μm using the QIAamp DNA FFPE Tissue Kit (Qiagen, Manchester, UK), following the manufacturer’s instructions. The concentration and quality of the DNA will be determined by the Agilent 2200 TapeStation system. To create the libraries, DNA samples (5 ng/µL) will be amplified using a primer, encoding the hypervariable regions V2-4-8 and V3-6, 7-9 of the bacterial 16 S rRNA using the 16 S Metagenomics Kit (Thermo Fisher, Waltham, MA, USA). The amplicons obtained will be purified using AMPure^®^ XP beads (Beckman Coulter, Pasadena, CA, USA) and, subsequently, the libraries will be created using the Ion Plus Fragment Library kit (Thermo Fisher, Waltham, MA, USA) and the Ion Xpress Barcode Adapters 1–16 kit (Thermo Fisher, Waltham, MA, USA) to add barcodes to purified amplicons. The libraries will be purified using AMPure^®^ XP beads (Beckman Coulter, Pasadena, CA, USA) and quantified by fluorescence. Sequencing of the libraries will be carried out using an Ion S5 platform. The results of composition, diversity, and richness will be analyzed using the QIIME2 platform, and functionality through the PICRUST software package.

#### 2.13.4. Analysis of Intestinal Permeability

Plasma levels of zonulin will be measured in duplicate using an ELISA commercial kit (IDK Zonulin ELISA, Immunodiagnostik AG, Bensheim, Germany), according to the manufacturer’s protocol.

#### 2.13.5. Determination of Endotoxemia Markers

LPS will be measured by using the Limulus Amebocyte Lysate Chromogenic Endpoint Assay (HycultBiotech, Uden, The Netherlands), following the manufacturer’s instructions.

#### 2.13.6. Determination of Inflammatory Markers

Markers of inflammation (IL-6, TNF-a, IL-1b, and IL-10) will be determined in serum by multiplex assay (Multiplex Human Cytokine MAGNETIC Panel, HCYTOMAG-60K, Merck Millipore, Burlington, MA, USA).

#### 2.13.7. Analysis of SCFAs in Fecal Samples by Gas Chromatography (GC) Coupled with a Flame-Ionization Detector

The levels of SCFAs in stool samples will be determined by GC coupled with a flame-ionization detector, as described elsewhere [22]. Briefly, 20 mg of fecal samples will be homogenized in 200 µL of distilled water and, subsequently, 100 μL of homogenized fecal samples will be mixed with 40 mg of sodium chloride, 20 mg of citric acid, 40 μL of 0.1 M hydrochloric acid, and 200 μL of butanol: tetrahydrofuran: acetonitrile (50:30:20). Samples will be vigorously vortexed and centrifuged at 14,870× *g* at room temperature for 10 min. The supernatant will be transferred to a new plastic tube, and 200 μL of a benzyl alcohol–pyridine mixture (3:2) and 100 μL DMSO will be added, and then vortexed for 5 s. Then, 100 μL of benzyl chloroformate will be added. To release the gases generated by the reaction, the tube lid will be kept open for 1 min. The tube will then be closed, and vortexed. After derivatization, 200 μL hexane will be added to the reaction mixture, and the sample vortexed for 5 min followed by a centrifugation step at 21,000× *g* for 2 min. Subsequently, 100 μL of derivative extract (upper hexane layer) will be transferred to a glass insert, and 5 μL injected in the GC-QqQ/MS in a split ratio of 25:1 using a fused-silica capillary DB-23 column Agilent 60 m × 0.25 mm (internal diameter) coated with a 0.15 μm thick layer of 80.2% 1-methylnaphatalene. Nitrogen will be used as the carrier gas at 1 mL/min (held for 4 min), reduced to 0.8 mL/min (held for 1 min) and then 0.6 mL/min (held for 1 min), and finally increased to 1 mL/min. The temperature of the FID detector will be adjusted and maintained at 260 °C, and the flow rates of H_2_, the air, and the make-up gas N_2_ to 30 mL/min, 350 mL/min, and 25 mL/min, respectively. The initial oven temperature will be set at 100 °C (held for 2 min), then increased to 200 °C at a rate of 15 °C/min, and finally maintained at 200 °C for 5 min. The identity of the SCFAs in the fecal samples will be confirmed through the comparison of their retention times and their mass spectra with those of the analytical commercial SCFA standards.

#### 2.13.8. Analysis of Plasma SCFA Levels by Ultra-High Performance Liquid Chromatography Tandem Mass Spectrometry (UHPLC-MS/MS)

For SCFA determination in plasma, 50 μL of plasma samples will be mixed with 10 μL of internal standard mixture (sodium acetate-13C2, propionic acid-d6 and butyric 1,2-13C2 acid) and 990 μL of methanol:water (50:50) mixture. Samples will be vortexed for 5 min and centrifuged for 5 min at 15,000 rpm and 4 °C. A volume of 80 μL of the supernatant will be mixed with 10 μL BHA 0.1 M and 10 μL EDC 0.25 M, vortexed and incubated at RT for 1 h in darkness to induce acid derivatization. After the incubation, serum extract will diluted 20-fold in methanol:water (50:50). Then, 200 μL of diluted sample will be extracted by 600 μL of diethyl ether through 10 min of vigorous shaking and centrifugation for 5 min at 20,000× *g* and 4 °C. After the centrifugation, 40 µL of the upper organic layer will be transferred and evaporated to dryness under a N_2_ flow and reconstituted in 200 µL of methanol:water (50:50) for UHPLC-MS/MS analysis.

The quantification of SCFA (acetic acid (AA), propionic acid (PA), butyric acid (BA), isobutyric acid (IBA), valeric acid (VA) and isovaleric acid (IVA)) will be performed by UHPLC coupled to triple quadrupole mass spectrometry using an UHPLC 1290 Infinity II Series coupled to a QqQ/MS 6490 Series (Agilent Technologies, Sta. Clara, CA, USA).

The chromatographic separation will be carried out with a gradient elution on a Kinetex polar C18 (100 × 2.1 mm, 2.6 µm) (Phenomenex, Torrance, CA, USA) column. The mobile phase will consist of 0.1% formic acid in water with 10 mM of ammonium formate (A) and 0.1% formic acid in methanol:2-propanol (9:1; *v*/*v*) (B). The gradient is as follows: 0 min 32% B, 4.6 min 60% B, 5.5 min 65% B, 7 min 98% B and 9 min 98% B, flow rate 0.3 mL/min, column temperature at 45 °C and injection volume 1 µL. The mass spectrometer operates via positive electrospray ionization, and data will be acquired in Multiple Reaction Monitoring (MRM) mode. Commercial standards will be used for the assignment and quantification of SCFA.

#### 2.13.9. Assessment of Postoperative Follow-Up and Recovery

Patients will be carefully monitored for any signs of anastomotic leak and surgical site infection symptoms (fever, leukocytosis, severe abdominal pain, etc.) within 30 days after surgery. Diagnosis of anastomotic leakage will be confirmed by radiological examination (CT scan or MRI), clinical examination, detection of serum biomarkers (CRP and procalcitonin), and post-operative endoscopy (if required). Post-operative surgical site infections will be assessed using the ASEPSIS score system. In addition, the recruited patients will be followed up for at least one year in order to evaluate recurrences of CRC, response to adjuvant therapy, and overall/disease-free survival.

Subjects will be followed up by phone every week during the intervention and for a month after surgery, and every month until the completion of the trial. Data collected from participants that withdraw from the study will be retained following the Office of Human Research Protections. No financial incentives will be provided to any of the participants.

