## Abstract

Colorectal cancer (CRC) is the third most common cancer and the second cause of cancer death worldwide. Several factors have been postulated to be involved in CRC pathophysiology, including heritable and environmental factors, which are the latest to be closely associated with nutritional habits, physical activity, obesity, and the gut microbiota. The latter may also play a key role in CRC prognosis and derived complications in patients undergoing surgery. This is a single-center, open, controlled, randomized clinical trial, in patients with scheduled surgical intervention for CRC. The primary objective is to assess whether a pre-surgical nutritional intervention, based on a high-fiber diet rich in polyunsaturated fatty acids (PUFAs), can reduce disturbances of the gut microbiota composition and, consequently, the rate of post-surgical complications in patients with CRC. Patients will be randomized in a 1:1 ratio after receiving a diagnosis of CRC. In the control arm, patients will receive standard nutritional recommendations, while patients in the intervention arm will be advised to follow a high-fiber diet rich in PUFAs before surgery. Participants will be followed up for one year to evaluate the overall rate of postsurgical complications, recurrences of CRC, response to adjuvant therapy, and overall/disease-free survival.

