## 2. Methods

### 2.1. Study Objectives

The objective of this study is to evaluate whether a pre-surgical nutritional intervention based on a high-fiber diet rich in PUFAs can revert gut microbiota alterations, surgical site infections, and anastomotic leaks in patients with CRC undergoing elective surgery (colonic resection with anastomosis), compared to a control group following standard nutrition recommendations.

To achieve this objective, three major aims are defined:To determine the change in the gut and intra-tumoral microbiome composition, fecal and serum levels of short-chain fatty acids (SCFAs), and serum inflammation, endotoxemia, and intestinal permeability markers in CRC patients following a high-fiber diet rich in PUFAs in the preoperative phase, in comparison to the control group.To evaluate the rate of anastomotic dehiscence and surgical site infections after surgery (30 days of follow-up) in the intervention group, in comparison to the control group.To establish the length of hospitalization, recurrences of CRC, response to adjuvant therapy, and overall and disease-free survival after surgery (1 year of follow-up) in the intervention group, in comparison to the control group.

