### 2.10. Participant Timeline

Individuals who agree to participate in this study will be assessed for eligibility. Eligible patients will be randomly assigned to the intervention or the control group (Figure 1). The trial will consist of a 4-week nutritional intervention pre-surgery, with a 12-month follow-up phase. The total trial period will be 13 months. A detailed assessment schedule can be found in Table 1.

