### 2.15. Statistical Methods

The analyses of this study will follow the intention-to-treat (ITT) principles. All statistical analyses will be performed with SPSS v.22.0 software (SPSS Inc., Chicago, IL, USA), considering a level of *p* < 0.05 as statistically significant. Normality of distributions will be assessed using the Shapiro–Wilk test. A descriptive analysis of the variables will be carried out with punctual estimation and a confidence interval for 95% of security, treating the continuous variables as means, standard deviation, or medians according to the distribution of the variable. Categorical variables will be presented in frequencies and percentages. Continuous variables will be compared by Student’s “t” test and by analysis of variance (ANOVA), depending on the existence of 2 or more groups in each comparison. The association between categorical variables will be analyzed using the chi-square test. Studies of correlations between the variables will be carried out using the Pearson or Spearman test based on the normality of the analyzed variables.

Per protocol analysis will be performed within participants that fulfill the intervention. This approach will be used only for the primary outcomes and will be treated as a secondary analysis. In the case of a relevant number of missing values, multiple imputation or pattern mixture models will be used.

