## Figures and Tables

**Figure 1 jcm-11-03613-f001:**
[figure not shown]
Trial flowchart of the intervention.

**Table 1 jcm-11-03613-t001:** Assessment schedule.

	STUDY PERIOD						
	Enrolment	Allocation	Post-Allocation				Close-Out
TIMEPOINT	t_−1_	t_0_	t_1_	t_2_	t_3_	t_4_	t_5_
ENROLLMENT:							
Eligibility screen	X						
Informed consent	X						
Inclusion criteria	X						
Exclusion criteria	X						
Allocation		X					
INTERVENTIONS:							
High-fiber diet rich in PUFAs			X	X			
Standard nutritional recommendation			X	X			
ASSESSMENTS:							
Anthropometric measurements	X						
Medication	X						
Food Frequency Questionnaire (FFQs)	X						
Tumor biopsies		X		X			X
Fecal samples			X	X			X
Blood samples			X	X			X
Anastomotic leak					X		
Surgical site infections					X		
CRC recurrence						X	
Response to adjuvant therapy						X	
Disease-free survival						X	
Quality of life questionnaire						X	

t_−1_: At baseline colonoscopy; t_0_: At baseline screening colonoscopy; t_1_: Four weeks pre-surgery intervention; t_2_: Day before surgery; t_3_: 30 days post-surgery; t_4_: 1–12 months after surgery (follow-up); t_5_: 12 months after surgery.

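### Follow-up for recurrence, disease-free survival and overall survival ends at 12 months in most places but is open-ended in Section 2.13.9, and the listed tests use neither follow-up time nor censoring

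*Protocol article*

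**What the plan says.** All places are in the protocol article.

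**End of follow-up fixed at one year**
- Abstract: "Participants will be followed up for one year to evaluate the overall rate of postsurgical complications, recurrences of CRC".
- Section 2.1, third aim: "overall and disease-free survival after surgery (1 year of follow-up) in the intervention group, in comparison to the control group". This also sets surgery as the origin.
- Section 2.10: "with a 12-month follow-up phase. The total trial period will be 13 months".
- Table 1: the close-out column t5 is defined as 12 months after surgery.

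**End of follow-up left open**
- Section 2.13.9, which describes how these outcomes are assessed: "the recruited patients will be followed up for at least one year in order to evaluate recurrences of CRC". The same section plans monthly calls up to an end of the trial that is not dated.
- Section 2.9 lists survival rates as a secondary outcome without a time point.

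**Completeness of follow-up**
- Section 2.8: patients who drop out are neither followed further nor replaced.
- Section 2.11: 10% losses are expected, which takes 48 per group to 54.

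**Schedule and analysis**
- Table 1 has rows for recurrence and disease-free survival, but none for death or overall survival.
- Section 2.15 names the t test and ANOVA for continuous variables and Pearson or Spearman correlation. For categorical variables it says: "The association between categorical variables will be analyzed using the chi-square test". It mentions multiple imputation or pattern mixture models if many values are missing.

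**The concern.** A minimum with no maximum is not the same as a 12-month phase inside a 13-month period. If observation runs to a common end of the trial, early recruits are watched longer than late ones. A recurrence at month 20 would then count in an early recruit and could not be seen in a late one. A proportion compared by chi-square over such data is neither a 1-year rate nor a rate over any common window.

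The two weaknesses reinforce each other. A time-to-event estimate read at 12 months is unaffected by longer observation, but a crude proportion is not. The trial is also unblinded (Section 2.12), so a cut-off that is not fixed in advance can be chosen after the data have been seen. Without a row for death in Table 1, the schedule does not show where one of the named outcomes is recorded.

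**Working it through.** **1. The plan's own figure.** The article gives no event count, event rate or power for recurrence or survival, so there is nothing to reproduce. The 54 per group used below comes from the leak calculation in Section 2.11 (48/0.90 = 53.3, rounded up to 54).

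**2. The passages side by side.**

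| Place | Origin | End |
|---|---|---|
| Abstract | not stated | one year |
| Section 2.1, third aim | surgery | one year |
| Section 2.10 | after the 4-week intervention | 12 months, 13 in total |
| Table 1, t5 | surgery | 12 months |
| Section 2.13.9 | not stated | one year as a minimum, no maximum |

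The conflict is in the end of follow-up, and Section 2.13.9 stands alone.

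**3. What an open end does to a crude proportion.** The documents give no event rate and no accrual length, so both are assumed here. Let the hazard be constant with 1-year risk p, so that λ = −ln(1 − p) per year. Let follow-up be spread evenly between 1 and 1 + A years. The expected crude proportion with an event is

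1 − [e^(−λ) − e^(−λ(1+A))] / (λA).

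For p = 0.10, λ = 0.10536, and e^(−λ), e^(−2λ), e^(−3λ) are 0.90, 0.81 and 0.729.
- A = 1 (12–24 months): 1 − (0.90 − 0.81)/0.10536 = 1 − 0.8542 = 14.6%.
- A = 2 (12–36 months): 1 − (0.90 − 0.729)/0.21072 = 1 − 0.8115 = 18.9%.

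| Assumed 1-year risk | Fixed 12 months | 12–24 months | 12–36 months |
|---|---|---|---|
| 5% | 5.0% | 7.4% | 9.7% |
| 10% | 10.0% | 14.6% | 18.9% |
| 15% | 15.0% | 21.5% | 27.4% |

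At 10% risk this is about 5.4, 7.9 and 10.2 events among 54 patients. Over the table the shift runs from 2.4 points (7.4 − 5.0) to 12.4 points (27.4 − 15.0).

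**4. Does the shift differ between arms?** Patients are randomized 1:1 as they are recruited, so both arms have the same expected distribution of follow-up. Under equal risk, each row of the table applies to both arms. Only a chance imbalance in recruitment timing could carry it into the comparison.

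**5. Losses within a fixed 12 months.** A patient lost event-free at month 4 has an unknown 12-month status, and a chi-square test must either drop that patient or count the patient as event-free. In the extreme case that all 10% are lost at once and counted event-free, a 10% risk is read as 0.90 × 10% = 9%. This is a smaller effect than the open end, and censoring deals with it directly.

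**The case against.** **The text can be read as consistent.** A minimum of one year is compatible with analysis at one year. Section 2.13.1 puts the last data and sample collection one year after surgery, t5 is at 12 months, and the 13 months in Section 2.10 read as a per-patient period. No passage describes a common calendar cut-off. This makes 12 months the likeliest intention. It does not remove the conflict, because the section that governs these outcomes states no maximum and Section 2.9 gives no time point.

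**The statistics section is a general list.** It assigns no test to recurrence or survival, and a survival method may sit in an analysis plan that is not shown. Its absence alone is therefore no error. What stands is that the tests stated do not fit the outcomes stated. The provision for imputation could help with dropouts, but it applies only when many values are missing and does not set the window.

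**Stronger readings the documents do not support**
- A reader might infer from the t4 label, "1–12 months after surgery (follow-up", that follow-up starts at month 1 and early deaths are lost. Section 2.1 counts from surgery, the label reads as the assessment period after the 30-day visit, and Section 2.13.9 plans weekly calls in the first month. Any share of deaths lost would rest on mortality figures the article does not give.
- A reader might infer that the true 1-year rates change. A rate cut at 12 months does not change when observation continues; only a crude proportion over all follow-up does.
- A reader might infer bias between arms. Step 4 shows that the shift is expected in both alike.
- A reader might want recurrence analysed with death as a competing event. At assumed 1-year recurrence of 10–15% and competing death of 3–5%, the gap from one minus Kaplan-Meier is only 0.2–0.4 points, so this is a preference and no part of the point.

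**Conclusion.** The point holds in limited form. The end of follow-up for three secondary outcomes is stated inconsistently, and the listed tests would not protect the analysis if the open-ended wording were followed. The consequence is a proportion that cannot be read as a 1-year rate, and a cut-off left open in an unblinded trial.

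The size is illustrative: at an assumed 10% 1-year risk, about 14.6% or 18.9% instead of 10%, depending on whether follow-up spreads over 12–24 or 12–36 months. These figures need a constant hazard, evenly spread follow-up, observation to a common end and crude counting, none of which the documents state. The 30-day leak and infection comparison and the sample size are untouched. It should still be corrected, because the conflict is plain in the text and the repair costs almost nothing.

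**What to change.** 1. **One window.** Reconcile the Abstract, Sections 2.1, 2.10 and 2.13.9 and Table 1 to one origin (the day of surgery) and one analysis cut-off at 12 months. In Section 2.13.9, replace the open minimum with 12 months and label any later data descriptive.
2. **Table 1.** Add a row for death and overall survival that covers the whole period from surgery to t5.
3. **Section 2.15.** For recurrence, disease-free survival and overall survival, name Kaplan-Meier 12-month estimates with 95% confidence intervals and a log-rank or Cox comparison. Censor at dropout or at 12 months, whichever comes first.

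**Cost.** These are wording changes only. Weekly calls in the first month, monthly calls after that and the 12-month close-out are already planned, so no visits are added. The one downside is that events after 12 months leave the formal comparison.

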### 2.14. Data Management

All the data generated from the project will be entered by two independent researchers of the team into an excel sheet. Files will then be double-checked for potential errors by a third independent researcher. Only individuals authorized by the Principal Investigator will have access to the data. Files will be uploaded to a clinical trial repository (e.g., Vivli, https://vivli.org/ (accessed on 20 April 2022)) and retained for up to 15 years after the end of the project.

